**Primary outcome**					
** Distress Thermometer**	DT	X		X	X
**Secondary outcomes**					
** Depressed** m**ood**	PHQ-9	X		X	X
** Anxiety**	GAD-7	X		X	X
** Traumatic distress**	IES-R	X		X	X
** Mini**-**Mental adjustment to cancer**	Mini-MAC	X		X	X
**Other variables**					
** Patient demographics**		X			

### Sample size *{14}*

Sample size was estimated using a target power of 80%, at a type I error rate of 0.05, and was calculated relative to the primary outcome measure; distress rating on the 11-point Distress Thermometer (DT) scale. The statistical test assumed was an independent samples *t*-test for group differences in the change from baseline to subsequent assessment, assuming that the randomisation ensures no systematic baseline or other covariate group differences. The minimal clinically significant difference for the DT is estimated to be 1 unit (standard deviation of improvement of 2 units), similar to other 11-point Likert scale questionnaires [30]. Calculation produced a suggested sample size of 64 per group. Allowing for a potential attrition rate of 20%, our final sample size is 80 participants per group (8 groups of 10).

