#### Implementation *{16c}*

Patients will be randomised after they are enrolled in the study, having consented and completed the Distress Thermometer (and scored ≥ 4). The research assistant will enter a participant’s baseline data into the research electronic data capture (REDcap) database, a randomisation button will allocate the participant to one of two study arms. Once a participant is randomised, it is not possible to undo this step. After 10–12 participants are enrolled for the interventional group, the psychological group will commence.

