### Statistical methods

#### Statistical methods for primary and secondary outcomes *{20a}*

Outcome analyses will be performed by a dedicated biostatistician. An intention-to-treat analysis will be performed on all randomised patients and a per-protocol analysis will be performed on all patients who complete the study. Descriptive statistics will be calculated for all outcome measures at each time point. Continuous variables will be reported using means, medians, standard deviations and score ranges. Categorical variables will be described using frequencies and percentages.

Descriptive and inferential statistics will be obtained using the appropriate statistical methods that seek to address our identified objectives. The primary analysis will compare the effect of the interventions on the primary outcome; distress levels at 12 weeks post-completion of the intervention period (i.e. c18 weeks post-baseline). All outcome analyses will be conducted according to an intention-to-treat principle, i.e. all randomised participants will be included in the main analysis and will be analysed as randomised, regardless of protocol adherence. Secondary analysis will include the analysis of the primary outcome post-intervention and analysis of the secondary and treatment process outcomes detailed previously post-intervention and at the 12-week follow-up. Linear mixed models on the outcome measures over time will be fitted to evaluate the effect of both study conditions, which intrinsically adjusts for baseline scores.

Statistical significance will be assessed from a *p* value < 0.05 from the group by time interaction term. For all tests, two-sided *p* values will be used, which will be reported to four decimal places with *p* values < 0.001 reported as *p* < 0.001. The Bonferroni method will be used to appropriately adjust the overall level of significance for multiple secondary outcomes as applicable. In the case of a significant result, planned contrasts of the group effects at the post-treatment period and at the 12-week follow-up will be used to investigate the direction and pattern of effects and outlined in advance in the SAP. As a key component of the reporting of the analyses of outcomes, the mean changes (irrespective of statistical significance) and correlations of the measures between the assessment time periods will be obtained. SPSS will be used to conduct the analyses.

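### Section {14} sizes the trial as if all patients were independent, although the intervention arm is treated in about 8 shared therapy groups, so the stated 80% power has no margin for within-group correlation

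*Protocol article*

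**What the plan says.** In Sample size {14}, the inputs are complete. "Sample size was estimated using a target power of 80"%, "at a type I error rate of 0.05". The minimal clinically significant difference is "estimated to be 1 unit (standard deviation of improvement of 2 units"). "The statistical test assumed was an independent samples" t-test on change from baseline. The result is 64 per arm, raised for 20% attrition: "our final sample size is 80 participants per group (8 groups of 10"). In that sentence the first use of group means trial arm and the second means therapy group. No ICC, design effect or other allowance for therapy groups appears.

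Intervention description {11a} has the intervention delivered in group sessions over six weeks, all by one psychologist. Implementation {16c} gives the way groups form: "After 10–12 participants are enrolled for the interventional group, the psychological group will commence". The control arm receives treatment as usual and is not grouped.

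Statistical methods {20a} plans the analysis in one line: "Linear mixed models on the outcome measures over time will be fitted to evaluate the effect of both study conditions". Tests are two-sided ("For all tests, two-sided"). Random effects are not listed, and therapy group is neither included nor excluded. The section refers to a statistical analysis plan, which is not shown.

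**The concern.** Patients in the same therapy group share sessions, fellow members and calendar time, so their outcomes may be correlated. The intervention-arm mean then rests on about 8 clusters (about 7 if groups have 12: 80/12 = 6.7) rather than on 80 independent patients, and its variance is larger than the t-test assumes. The control-arm mean is unaffected.

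This has two consequences. The power stated in {14} rests on a variance that does not match the design in the same paragraph. And if the analysis also ignores therapy group, the standard error of the primary effect is too small and the p-value too favourable. The protocol's introduction says that a positive result would be the basis for national roll-out, so the calibration of that p-value matters.

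**Working it through.** **Inputs from the protocol.** Two-sided alpha 0.05, power 80%, difference 1, SD of change 2, 1:1 allocation, 20% attrition, 8 therapy groups of 10. With 20% attrition this leaves 8 groups of m = 8 completers (n_T = 64) and n_C = 64 controls. **Assumed:** ICC 0.01, 0.05 or 0.10, because the documents give none.

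**1. Reproduce the plan's figure.** Standardised difference 1/2 = 0.5. The exact two-sided t-test needs 63.8, so 64 per arm, with power 80.1%. 64/0.8 = 80. Both stated figures reproduce under independence.

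**2. Variance with clustering in one arm.**

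V_T = 4 × [1 + (m − 1) × ICC]/64, V_C = 4/64 = 0.0625, SE = √(V_T + V_C).

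At ICC 0.05: V_T = 4 × 1.35/64 = 0.0844, and SE = √0.1469 = 0.383, against √0.125 = 0.354 under independence.

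**3. Power.** Normal approximation: Φ(1/SE − 1.96). Small-sample version: noncentral t with noncentrality 1/SE and Satterthwaite df = (V_T + V_C)² / [V_T²/7 + V_C²/63], where 7 = 8 − 1 groups and 63 = 64 − 1 controls.

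**4. Type I error if therapy group is left out of the model.** 2 × [1 − Φ(1.96 × 0.354/SE)].

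| ICC | SE | df | Power, normal | Power, Satterthwaite | Type I error, groups ignored |
|---|---|---|---|---|---|
| 0 | 0.354 | 25.2 | 80.7% | 77.6% | 5.0% |
| 0.01 | 0.360 | 23.9 | 79.4% | 76.0% | 5.4% |
| 0.05 | 0.383 | 20.0 | 74.2% | 69.9% | 7.1% |
| 0.10 | 0.411 | 17.0 | 68.2% | 63.1% | 9.2% |

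A simulation with 40,000 runs per ICC gave type I errors of 5.5%, 7.2% and 9.0% for ICC 0.01, 0.05 and 0.10.

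The row at ICC 0 separates two effects. Modelling 8 clusters costs about 3 points of power through the degrees of freedom even when there is no correlation (80.7% to 77.6%). The rest of the fall comes from correlation.

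**5. If nobody drops out** (8 groups of 10, 80 controls), Satterthwaite power is 84.3% / 77.4% / 69.3% for the three ICCs.

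**6. Baseline adjustment.** With equal variances at baseline and follow-up, the change score has variance 2σ²(1 − r) and an ANCOVA-type analysis has σ²(1 − r²), a ratio of (1 + r)/2. The baseline correlation r is assumed, and the ICC is taken as unchanged. Satterthwaite power at 64 per arm:

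| r | ICC 0.05 | ICC 0.10 |
|---|---|---|
| 0.5 | 81.7% | 75.5% |
| 0.7 | 76.8% | 70.2% |

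**The case against.** The strongest reply is that the analysis half rests on silence. A reader might infer from {20a} that therapy group is excluded from the model, so that the 5% level is lost. The documents do not support that. The section lists no random effects at all, and random-effects structure and degrees of freedom are ordinary content for the analysis plan. The type I error figures are therefore conditional on the term being absent there too. This part of the reply stands.

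Second, the ICC is assumed. One psychologist delivers every group, which removes between-therapist variance; the six-session programme is common to all groups; and the primary assessment is 12 weeks after the last session. Each could keep the ICC low, and near 0.01 the loss is small. That stands as a limit on the size. But none of these features removes shared group composition, interaction or timing, and zero correlation remains an unstated assumption.

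Third, part of the lower Satterthwaite power is the price of the recommended analysis and not of correlation, and attrition below 20% would help. Both are true, and the working shows both.

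The reply does not reach the sample size statement itself. Section {14} gives its test, its inputs and its number of therapy groups, and the test does not fit those groups.

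**Conclusion.** The point holds for the sample size and, conditionally, for the analysis. The 80% in {14} is correct only if outcomes within a therapy group are uncorrelated and the analysis does not model the groups. At the planned attrition and on the plan's own change-score basis, any positive ICC takes power below 80%: slightly at 0.01 (79% normal, 76% Satterthwaite), materially from about 0.05 (74% and 70%), and to 68% and 63% at 0.10. These figures rest on the assumed ICC range, equal groups of 8 completers, and the protocol's difference of 1 and SD of 2.

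If therapy group is left out of the final model, type I error would be about 5.4% to 9.2% over the same range. If it is modelled, the 5% level can be kept, at the cost in power shown above.

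A reader might also infer that the sample must be enlarged, or that baseline adjustment makes the problem disappear. Neither follows from the documents. Adjustment recovers much of the loss, but whether it restores 80% depends on a baseline correlation that the protocol does not state.

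**What to change.** 1. Make sure that therapy-group ID is recorded in REDCap for every intervention patient. The protocol reports 8.5% recruited, so this can be done prospectively.
2. In {20a}, specify a random effect for therapy group in the intervention arm only, with no such effect for controls, and Satterthwaite or Kenward-Roger degrees of freedom. Confirm that the analysis plan says the same.
3. In {14}, replace the unqualified 80% with the power over a stated ICC range for the analysis actually planned. For a change-score analysis at 64 per arm with Satterthwaite degrees of freedom, this is about 76% / 70% / 63% at ICC 0.01 / 0.05 / 0.10. If a baseline-adjusted analysis is planned, state the assumed baseline correlation and give the power on that basis.

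The cost is some wording, one data field and one model term. The stated power becomes less favourable and the confidence intervals somewhat wider. If the sponsor wants 80% on the change-score basis instead, whole groups of 8 completers would require 9 / 10 / 12 groups at the three ICCs. That means 72 / 80 / 96 evaluable and, dividing by 0.8, 90 / 100 / 120 recruited per arm, against the 80 planned.

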### Recruitment *{15}*

Adult patients who are attending the MMUH Cancer outpatient clinics, for the management of cancer recurrence that has occurred since March 2020, who are proficient in the English language will be eligible for consideration. Potentially eligible candidates will be informed of the study at the outpatient clinics of the Cancer and Surgical Directorate, and those expressing initial interest will be provided with a participant information leaflet (PIL) to read. They will also be given a consent form should they wish to participate after reading the PIL.

These individuals will then be followed up with a screening call by the research assistant allied to the research team or if present in the clinic, the research assistant will be on hand to discuss in person. All patients entering the screening phase of the study will be registered on a Study Patient Registration Log and a unique registration number will be assigned. Clinical data will be assessed to evaluate a subject’s eligibility and only those who endorse a score of ≥ 4 on the Distress Thermometer will proceed for study enrolment. Enrolled patients will be evaluated and asked for informed consent, by way of a signed, returned, consent form, after which time they will be randomly allocated to one of two study conditions.

### Assignment of interventions: allocation

#### Sequence generation *{16a}*

A computer-generated randomisation process will be used to allocate the participant to either compassion-focussed therapy and breathing pattern retraining groups or TAU with a 1:1 allocation. It is a feature of the research electronic data capture (REDcap) software being used in this study. The randomisation list will consist of blocks of variable size, with equal allocation to arms within each block.

#### Concealment mechanism *{16b}*

Once baseline data is obtained, it will be entered into research electronic data capture (REDcap), a secure, browser-based web application widely used by researchers for survey data collection. Allocation sequence concealment is a core, automated feature of this software program, which will prevent the participants and researchers from being aware of the generated sequence until after participants are assigned to their groups.

#### Implementation *{16c}*

Patients will be randomised after they are enrolled in the study, having consented and completed the Distress Thermometer (and scored ≥ 4). The research assistant will enter a participant’s baseline data into the research electronic data capture (REDcap) database, a randomisation button will allocate the participant to one of two study arms. Once a participant is randomised, it is not possible to undo this step. After 10–12 participants are enrolled for the interventional group, the psychological group will commence.

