**Methods:**

This is a single-centre, prospective, randomised controlled trial. Patients identified as having experienced cancer recurrence since March 2020 (the onset of the COVID-19 pandemic in Ireland) will be screened for participation. Eligible, consenting candidates who score 4 or higher on the Distress Thermometer will be enrolled in the study. Participants will be randomly allocated to receive either a 6-week, group-based, online, compassion-focussed therapy and breathing pattern retraining intervention or the control arm. Those in the control arm will all be offered the group intervention after the 18-week study period. The primary outcome is the Distress Thermometer score at 18 weeks post-baseline though secondary outcomes will include measures of mood, traumatic distress and mental adjustment to cancer.

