### Trial design *{8}*

The COMFORT trial is designed as a prospective, randomised, controlled, single-centre superiority trial with two parallel groups and a primary endpoint of psychological distress 18 weeks post-enrolment. The study will randomise patients who have experienced a cancer recurrence since March 2020 into two groups on a 1:1 basis: one that receives compassion-focussed therapy and radical breathing retraining and the other control group who receives TAU. As all patients will be endorsing elevated levels of distress, it is possible that they will be indicated for individual psychosocial care, as part of the hospital’s psycho-oncology service (CNS, Social Work, Psychology & Psychiatry), but this is likely to be controlled for across both groups. Figure 1 illustrates the study design, timelines of the intervention and baseline as well as follow-up evaluations. The estimated duration for the main investigational plan (e.g. from the start of screening of the first participant to the last participant processed and finishing the study) is 15–18 months.

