### Strategies to improve adherence to interventions *{11c}*

All participants for this trial will be eligible to receive the psychological and breathing interventions (see the ‘Intervention description {11a}’ section). Those in the treatment arm of the study will be offered the intervention immediately after enrolment and those in the control arm of the study will have the option of completing the group programme once the study period has been completed. Additional measures to aid adherence include its virtual format, ensuring there are no geographical barriers precluding someone from participating. Moreover, the group sessions will only last approximately 90 min, inclusive of a break, to minimise the content burden. All participants will also be well-informed during the consent process. The study participation burden, such as completion of primary outcome questionnaires at t(0) (baseline), t(1) (post-6-week group intervention) and t(2) (3 months post-intervention period), post-enrolment will be explained. The research assistant responsible for screening potential study participants will record all eligible candidates and those that do not proceed with the study due to ineligibility, non-consent or withdrawal. In so far as it is possible, only eligible and fully willing individuals will proceed to randomisation and allocation of the patient to either the CFT and BPR or control groups.

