### Outcomes *{12}*

#### Primary outcome

Distress Thermometer Likert scale score [time frame: 3 months after completion of the 6-week group intervention]

The Distress Thermometer (DT) assessment tool will be used to assess for psychological distress levels at the appropriate study time points. This assessment will be conducted by the research assistant. Its scale is measured between ‘0’ and ‘10’, where ‘0’ indicated no distress and ‘10’ indicates extreme distress. A decrease on the DT score of 1 unit (standard deviation of improvement of 2 units) is considered clinically significant and can indicate an improvement in a person’s psychological distress levels [13].

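### The primary time point has three incompatible origins, and the wait for a therapy group to fill may put the two arms on different clocks

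*Protocol article*

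**What the plan says.** **Randomisation and start of treatment.** Allocation is individual and follows baseline data entry: "The research assistant will enter a participant’s baseline data into the research electronic data capture (REDcap) database, a randomisation button will allocate the participant" (Implementation {16c}). The same section then makes the therapy group wait: "After 10–12 participants are enrolled for the interventional group, the psychological group will commence". The adherence section {11c} says otherwise: "Those in the treatment arm of the study will be offered the intervention immediately after enrolment". The retention section {18b} describes an 18-week commitment made up of 6 weeks of therapy and 12 of follow-up, which leaves no time for a group to fill.

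**Primary time point.**
- Abstract: "The primary outcome is the Distress Thermometer score at 18 weeks post-baseline".
- Trial design {8}: "a primary endpoint of psychological distress 18 weeks post-enrolment".
- Outcomes {12}: "time frame: 3 months after completion of the 6-week group intervention".
- Statistical methods {20a} treats the last two as the same: "distress levels at 12 weeks post-completion of the intervention period (i.e. c18 weeks post-baseline".
- Objectives {7} counts three months from randomisation.

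**Visits.** Table 2 has one baseline, at enrolment, and labels both follow-up columns by reference to the group. It has no separate schedule for controls and no repeat baseline when a group starts.

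**The concern.** The primary test is the group-by-time interaction in a linear mixed model. If the final visit means a different elapsed time in each arm, that offset enters the interaction together with the treatment effect, and randomisation does not remove it. Patients enter with a Distress Thermometer (DT) score of 4 or more after a recurrence, so distress may change over time through adaptation or disease progression, whatever the treatment. A longer clock in one arm would also give that arm more time to lose patients to illness or death, while the plan makes a single 20% attrition allowance for both arms. Unequal visit timing cannot be undone once the data are collected.

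**Working it through.** **1. Planned size.** A two-sided t-test at 0.05 with 80% power, difference 1 and SD 2, needs 63.8, so 64 per arm. Then 64 / 0.80 = 80 per arm. The protocol's figures reproduce and are not affected by this point.

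**2. The origins compared.** Let W be the weeks from a patient's baseline to the start of the group. In the intervention arm, counted from the end of the group:
- final assessment = W + 6 + 12 = 18 + W weeks after baseline.
- This equals 18 only if W = 0, which is about right for the last patient to join a group and for no one else.
- Three months (about 13 weeks) from randomisation would fall 13 − 6 − W weeks after the group ends: 7 weeks if W = 0, and 3 to 4 weeks if W is 3 to 4. It does not match the 12 weeks in the other sections.

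**3. Length of the wait.** Inputs:
- 80 intervention patients (Sample size {14}).
- Group size k of 10 to 12 (Implementation {16c}; the sample size section plans 8 groups of 10).
- Recruitment of just under 12 months (section {21a}), or 25 August 2022 to September 2023 (Trial status), taken as 52.2 to 57.3 weeks.
- Steady accrual, which is my assumption; the protocol gives no accrual rate and no maximum wait.

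Weekly rate r = 80 / recruitment weeks. Mean wait = (k − 1) / (2r). Wait of the first to enrol = (k − 1) / r.

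| Recruitment (weeks) | r | k | Mean wait | Longest wait | Final visit, mean | Final visit, latest |
|---|---|---|---|---|---|---|
| 52.2 | 1.53 | 10 | 2.9 | 5.9 | 20.9 | 23.9 |
| 52.2 | 1.53 | 12 | 3.6 | 7.2 | 21.6 | 25.2 |
| 57.3 | 1.40 | 10 | 3.2 | 6.4 | 21.2 | 24.4 |
| 57.3 | 1.40 | 12 | 3.9 | 7.9 | 21.9 | 25.9 |

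All waits and visits are in weeks. If recruitment took 9 months, the mean wait would be 2.2 to 2.7 weeks; if 18 months, 4.4 to 5.4 weeks.

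**4. What this means for the comparison.**
- *Controls counted from their own baseline.* This is the literal reading of the Abstract and Trial design. Controls are seen at 18 weeks and intervention patients at about 21 to 22 on average. W is never negative, so the gap always runs the same way.
- *Controls seen alongside the concurrent group.* Controls who enrol while the group fills wait about as long, so the systematic gap largely disappears. The stated 18 weeks is then wrong in both arms.

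**The case against.** The strongest reply is that nothing shows controls to be assessed earlier. A reader might infer from the 18-week wording that the arms are certainly compared weeks apart, but the article never gives the control arm's origin. Table 2's group-based column labels and the approximate 18 weeks in {20a} fit equally well with controls being seen alongside the concurrent group. Figure 1, which is said to show the timelines, is not available here, and a full protocol may carry the scheduling rule. This stands: the gap between arms is conditional.

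A reader might also want to put a figure on the bias. That needs a weekly drift in untreated distress, which the document does not give. As illustration only, an assumed drift of 0.02 to 0.05 points a week over 3 to 4 weeks would give 0.06 (0.02 × 3) to 0.20 (0.05 × 4) points. The standard error of the difference is 2 × √(2/64) = 0.35. Regression to the mean should appear mostly at the first re-measurement rather than build up between weeks 18 and 21. So no bias figure should be reported as a finding.

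The reply does not remove the contradiction. The stated origins cannot be met together whichever way controls are scheduled, and the two statements about when treatment starts conflict on their face.

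**Conclusion.** The point holds as a contradiction in the definition of the primary time point, with a conditional threat to the comparison. For most intervention patients the final assessment cannot be both 18 weeks after baseline and three months after the group ends, and three months from randomisation fits neither. Under steady accrual over 52 to 57 weeks, the intervention visit falls about 3 to 4 weeks later than stated on average, and about 6 to 8 weeks later for the first to join a group. A difference of 3 to 4 weeks between arms follows only if controls are counted from their own baseline. The document neither confirms nor excludes that, and the direction and size of any resulting bias cannot be derived from it.

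**What to change.** State one origin that applies identically to both arms.
- At randomisation, link each control to the intervention group then filling, and schedule that control's two follow-up visits in the same calendar windows as the group's.
- Keep the pre-randomisation assessment as baseline in both arms.
- Record actual weeks from randomisation to each assessment and use them in a sensitivity analysis.
- Restate the primary time point to match, and reconcile the Abstract, {7}, {8}, {11c}, {12}, {16c}, {18b} and {20a}. The conflicting statements on when treatment starts also need to be reconciled; which one is right is for the investigators to say.

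**Cost.** A scheduling rule and an amendment. Control visits would depend on group start dates, and some controls would be followed somewhat beyond 18 weeks. If the 8.5% already recruited refers to the target of 160, about 14 patients (0.085 × 160 = 13.6) entered under the present wording; their actual visit times should be recorded too.

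**Alternatives.** Randomising in batches just before each group would also align the clocks. It moves the wait and any losses to before randomisation, may leave some patients below the entry score when baseline is taken, and changes the procedure during enrolment. A repeat baseline after allocation should not replace the pre-randomisation one: the trial is unblinded, and patients who know their arm may score differently.
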